**Number of subjects**

Reilly reported that outbreak of gene concerned with platelet which could increase risk of MI occurred at 3-6 days after operation in patients who received continuously aspirin until operating day before coronary artery bypass surgery. In the study, GPIIb, GpIIIa, COX-1 gene expression increased by 3 times in all of 11 patients compared to baseline. For OPCAB, there was no data on GpIIb, GpIIIa, COX-1 gene expression. Therefore, 20 subjects are needed for each group, that is, total of 40 subjects are needed for this study. Considering the loss rate of 20%, total of 48 subjects will be needed.

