**Randomization**

All subjects will be randomly assigned with 1:1 ratio to two groups as following:

- Control group: patients receiving low dose aspirin (100 mg/day) until operating day
- Study group: patients stop aspirin (100 mg/day) 4 days before surgery

Random sequence will be made by a study nurse with size 2 blocks (AA, AB, BA, BB) including letter of ‘A’ (meaning aspirin continuation group) and ‘B’ (meaning aspirin discontinuation group). And then each generated letter will be concealed in an envelope in the order of generation. Enrolled patients will be allocated to their groups depending on the letter (A or B) inside the concealed envelopes that will be opened by an anesthesiologist who was unaware of the study.

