**Study protocol**

Assigned ward nurses will deliver drugs to all patients during the perioperative period.

In the aspirin continuation group (n=24), aspirin (100 mg; aspirin protect®, Bayer AG, Leverkusen, Germany) will be administered every morning until the operative day.

In the aspirin discontinuation group (n=24), aspirin will be stopped 4 days before the operative day.

Other anticoagulants, such as clopidogrel or warfarin will be stopped at least 5 days before surgery in all patients.

Anesthetic and surgical techniques will be standardized during the trial. A single anesthesiologist and a single surgeon, not aware of the group assignment, will perform OPCAB in all patients. All patients will arrive in the operating room without premedication. A catheter will be inserted at radial artery after local anesthesia for continuous arterial blood pressure monitoring. And standard monitoring including ECG, NIBP, SpO_2_ and BIS monitoring. Anesthesia will be induced with 0.15 mg/kg midazolam, 1-2 μg/kg sufentanil and vecuronium. After endotracheal intubation, mechanical ventilation will be applied to maintain an end-tidal carbon dioxide tension of 35-40 mmHg. Anesthesia will be provided with target-controlled infusion of propofol and remifentanil.

Target activated clotting time (ACT) will be 250-350 s.

1.5 mg/kg unfractionated heparin will be administrated before making of Y-graft.

At following time points, blood will be sampled for evaluation of platelet activation and responsibility.

- T1. Before skin incision
- T2. After reperfusion of graft
- T3. End of surgery
- T4. 24 h postoperatively
- T5. 48 h postoperatively
- T6. 72 h postoperatively
- T7. 96 h postoperatively

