**Statistical analyses**

Statistical analyses will be performed with intention-to-treat.

If data will be normal distributed, we will use student t-test or Chi square test. Otherwise, Mann-Whitney test or Fisher’s exact test will be used.

For the primary outcome, increase of GPIIb mRNA, independent t-test will be used.

For the evaluation discrepancy of platelet mRNA expression by aspirin effect between two groups at each time points, we will use the generalized estimating equation/general linear model. P-value < 0.05 will be considered to be significant.

Repeated-measures analysis and Bonferroni correction will be used for adequate analysis between groups.

Data will be presented as mean ± Standard deviation, median [interquartile range], and number of patients (%). All statistical analyses will be performed with IBM SPSS Statistics software (version 21, SPSS Inc., IBM Corporation, USA).

References

1. Bernard Lo, Rob Fijnheer, Domenico Castigliego, Cornelius Borst, Cor J. Kalkman, Arno P. Nierich, Activation of hemostasis after coronary artery bypass grafting with or without cardiopulmonary bypass. Anesth Analg 2004; 99: 634-40

2. Alessandro Parolari, Luciana Mussoni, Marta Frigerio, Moreno Naliato et al., The role of tissue factor and P-selectin in the procoagulant response that occurs in the first month after on-pump and off-pump coronary artery bypass grafting. The journal of thoracic and cardiovascular surgery 2005; 130(6): 1561-1566

3. Raymond Cartier, Current trends and technique in OPCAB surgery. J Card Surg 2003; 18: 32-46

4. Frantisek Bendar, Pavel Osmancik, Tomas Vanek, Heidi Mocikova, Martin Jares, Zbynek Straka, Petr Widmsky , Platelet activity and aspirin efficacy after off-pump compared with on-pump coronary artery bypass surgery: results from the prospective randomized trial PRAGUE 11-Coronary Artery Bypass and Reactivity of Thrombocytes (CABARET). The journal of thoracic and cardiovascular surgery 2008; 136(4): 1054-1060

5. Robert Poston, Junyan Gu, James Brown, James Gammie, Charles White, Jeffrey Manchio, Richard N. Pierson et al., Hypercoagulability affecting early vein graft patency dose not exist after off-pump coronary artery bypass. J of cardiothoracic and vascular anesthesia 2005; 19(1): 11-18

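### The 20 per group is called needed but has no stated basis for a between-group comparison, and 48 patients fall slightly short of covering a 20% loss

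*Protocol*

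**What the plan says.** The section Number of subjects in the Protocol gives the whole justification in one paragraph. It describes a published series of coronary bypass patients who took aspirin up to the operating day and reports: "In the study, GPIIb, GpIIIa, COX-1 gene expression increased by 3 times in all of 11 patients compared to baseline". It then concedes: "For OPCAB, there was no data on GpIIb, GpIIIa, COX-1 gene expression". The next sentence draws the conclusion: "Therefore, 20 subjects are needed for each group, that is, total of 40 subjects are needed for this study". The allowance for loss follows: "Considering the loss rate of 20%, total of 48 subjects will be needed".

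The enlarged total is carried into the design. Under Randomization: "All subjects will be randomly assigned with 1:1 ratio to two groups as following". Under Study protocol each arm has 24 patients ("In the aspirin continuation group (n=24" and "In the aspirin discontinuation group (n=24").

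Statistical analyses assigns an independent t-test to the primary outcome, the increase in GPIIb mRNA, and sets a general level: "P-value < 0.05 will be considered to be significant". It does not say whether tests are one-sided or two-sided. The section Hypothesis expects the increase after stopping aspirin to be no higher than the increase with continued aspirin, and gives no margin.

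**The concern.** There are two separate issues, and the first matters more.

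**The inference.** A comparison of two randomised groups is sized from a between-group difference, a between-patient SD, a significance level and a power. The cited series offers a before-after change under one regimen, the one used in the control arm. It says nothing about how far the stopped-aspirin arm might differ, or how much patients vary. The absence of off-pump data removes the remaining link to the trial population. The paragraph still presents 20 per group as a consequence of these facts.

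**The loss allowance.** If 40 evaluable patients are needed and 20% are lost, 48 is not quite enough.

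The stake is how the result will be read. The hypothesis is one of no greater increase, without a margin. If readers believe the trial had the size it needed, a non-significant t-test will look like confirmation. Nothing in the Protocol tells them how large a difference such a result could conceal.

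**Working it through.** **Inputs from the Protocol.** Evaluable target 20 per group, 40 in total; loss rate 20%; total 48 (Number of subjects). Twenty-four per arm (Study protocol). Independent t-test and a 0.05 level (Statistical analyses). Not stated anywhere: power, between-group difference, SD, margin, sidedness.

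**Step 1: reproduce the stated total.** 40 × (1 + 0.20) = 48, or 24 per arm. This matches the Protocol exactly.

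**Step 2: check it against the stated loss.**
- Total needed so that 40 remain: 40/(1 − 0.20) = 50.
- Remaining from 48 at 20% loss: 48 × 0.80 = 38.4, or 19.2 per arm.
- Loss that 48 can absorb: (48 − 40)/48 = 8/48 = 16.7%.

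**Step 3: size of the slip.** Assume a two-sided 5% t-test, and that 20 per group gives 80% power. That corresponds to a difference of 0.909 SD. At the same difference, exact power is 78.3% with 19.2 per arm and 77.8% with 19. The loss is about two points. Put the other way, the difference detectable with 80% power moves from 0.909 SD (20 per arm) to 0.934 SD (19 per arm).

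**Step 4: try to reproduce 20 per group.** The normal-approximation formula is n per group = 2(z₀.₉₇₅ + z₀.₈₀)² (SD/δ)² = 2(1.960 + 0.842)² (SD/δ)² ≈ 15.7 (SD/δ)². The Protocol supplies neither δ nor SD, so no value follows. To show how much this leaves open, take δ = 200 percentage points purely as an assumption:

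| Assumed SD (percentage points) | n per group, 80% power |
|---|---|
| 100 | 4 |
| 200 | 16 |
| 225 | 20 |
| 300 | 36 |
| 400 | 63 |

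Twenty per group is one point on this range. The documents give no reason to prefer it or to reject it.

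**Step 5: what 20 per group delivers (two-sided 5% assumed).**
- Detectable difference by exact t-test: 0.91 SD at 80% power, 1.05 SD at 90%.
- If the 5% were one-sided, the normal approximation gives (1.645 + 0.842) × √(2/20) = 0.79 SD at 80% power, against 0.89 SD two-sided by the same approximation.
- Power for a true difference of 0.5 SD: 34%.
- 95% CI half-width for the difference: t₀.₉₇₅ with 38 df × √(2/20) = 2.024 × 0.316 = 0.64 SD.

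**The case against.** The strongest reply has three parts.

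First, the gap between 48 and 50 is two patients and about two points of power, in a plan that states no power target. That is right, and alone it would be an editorial correction. It is still worth making, because at the stated loss rate the stated total does not leave the stated 40.

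Second, the paragraph does not claim a power calculation, and a small mechanistic trial in a population without prior data may reasonably choose its size on other grounds. This is fair as far as it goes. However, the text gives no other grounds. It offers the cited series as the reason and calls the result a requirement.

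Third, a fuller derivation might sit in a statistical analysis plan that is not at hand. The point does not depend on something missing. It concerns an inference made in the Protocol itself, from premises that cannot carry it.

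Two stronger readings are tempting. A reader might infer that the sample size is wrong or that the trial is underpowered. The documents do not support this: without a difference and an SD, 20 per group cannot be checked, so it is unsupported rather than mistaken. A reader might also be struck that, with independent 20% losses, the chance of keeping at least 40 of 48 is only 36%. With 50 enrolled the same chance is only 58%, because 40 is then simply the expected number. Much of that apparent risk therefore comes from the demanding criterion, not from the slip.

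**Conclusion.** The concern holds in a limited form. The step from a one-regimen, within-patient rise in 11 on-aspirin patients to 20 per group does not follow, and nothing elsewhere in the Protocol supplies the missing difference, SD or power. This is a fault of justification and does not show that the number is too small.

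The loss allowance is a minor arithmetic slip: 48 covers a loss of 16.7%, not 20%, and at 20% about 38 patients remain (19 per arm).

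The practical consequence lies in interpretation. Under the assumed two-sided 5% t-test, differences well below 0.91 SD would often be missed. With no margin stated, a non-significant result cannot establish that the increase after stopping aspirin is no higher. The two-sided level and the 80% power are assumptions of this review; the Protocol states neither.

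**What to change.** Reword the paragraph under Number of subjects; the enrolment target can stay at 48.

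1. **Loss.** State that 48 randomised patients leave 40 evaluable at a loss of up to 16.7%, and about 38 (19 per arm) at 20%.
2. **Basis.** Replace the inferential sentence with a statement that 20 per group was not derived from between-group or off-pump data. The sponsor should then give the actual reason. The Protocol does not mention one (feasibility, for example), so a reviewer should not supply it.
3. **Precision.** Add that, assuming a two-sided 5% t-test, 20 per group has 80% power for a difference of about 0.91 SD (19 per group: 0.93 SD), with a 95% CI half-width of about 0.64 SD at 20 per group.
4. **Interpretation.** Add, with a cross-reference to Hypothesis, that no margin has been set and that a non-significant difference will not be taken as evidence that the increase after stopping aspirin is no higher.

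The cost is a few sentences, with no added patients or procedures. The stated figures become slightly less favourable.

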**Randomization**

All subjects will be randomly assigned with 1:1 ratio to two groups as following:

- Control group: patients receiving low dose aspirin (100 mg/day) until operating day
- Study group: patients stop aspirin (100 mg/day) 4 days before surgery

Random sequence will be made by a study nurse with size 2 blocks (AA, AB, BA, BB) including letter of ‘A’ (meaning aspirin continuation group) and ‘B’ (meaning aspirin discontinuation group). And then each generated letter will be concealed in an envelope in the order of generation. Enrolled patients will be allocated to their groups depending on the letter (A or B) inside the concealed envelopes that will be opened by an anesthesiologist who was unaware of the study.

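### The listed size-2 blocks include AA and BB, so they restrict nothing and do not deliver the planned 24 patients per group

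*Protocol*

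**What the plan says.** The Randomization section of the protocol sets the target ratio: "All subjects will be randomly assigned with 1:1 ratio to two groups as following". It then describes the list: "Random sequence will be made by a study nurse with size 2 blocks (AA, AB, BA, BB"), where A stands for continuing aspirin and B for stopping it. It adds that "each generated letter will be concealed in an envelope in the order of generation". No later step checks or restores balance, and nothing says how often each pair type is to be used.

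The Study protocol section gives the group sizes as fixed numbers: "In the aspirin continuation group (n=24") and "In the aspirin discontinuation group (n=24").

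The Number of subjects section gives the requirement behind them: "20 subjects are needed for each group, that is, total of 40 subjects are needed for this study". It then allows for loss: "Considering the loss rate of 20%, total of 48 subjects will be needed".

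**The concern.** Blocking exists to hold the two arms level. A block does this only if it contains as many A's as B's. For a block of two under 1:1 allocation, the only such blocks are AB and BA. AA and BB put two consecutive patients in the same arm. The four listed pairs are all the ordered pairs that two letters can form, so calling them blocks rules out no sequence.

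The Randomization section therefore does not produce the group sizes given in the Study protocol section. Whoever prepares the envelopes has to choose. Following the listed set allows unequal arms. Following the word blocks and the two figures of 24 means departing from the listed set. A later reader could not tell which was done, and an unequal list cannot be repaired once patients have been enrolled from it.

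**Working it through.** **Inputs.** From Number of subjects: 20 per group, 40 in total, 20% loss, 48 to be randomised. From Study protocol: 24 per group. From Randomization: 1:1 ratio and the pairs AA, AB, BA, BB. One assumption is needed because the protocol gives no draw rule: the pairs are drawn independently, each with probability 1/4.

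**The plan's own figure.** 40 × 1.20 = 48, and 48 / 2 = 24 per group, as stated. (Dividing by the retained fraction gives 40 / 0.80 = 50; nothing below depends on this.) The figure of 20 per group cannot be reproduced, since no effect size, standard deviation or power is given.

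**Do the pairs restrict the sequence?** P(second letter is A, given first is A) = P(AA) / [P(AA) + P(AB)] = 0.25 / 0.50 = 0.50. The second letter is independent of the first. The number of A's in 24 such pairs was computed exactly and is identical to a Binomial(48, 0.5) count.

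**Distribution of the split.** With X the number of A's, P(X = k) = C(48, k) / 2^48.

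| Event | Probability |
|---|---|
| Exactly 24:24 | C(48, 24) / 2^48 = 11.5% |
| Not 24:24 | 88.5% |
| 21:27 or worse | 47.1% |
| 20:28 or worse | 31.2% |
| One arm below 20 before any loss (19:29 or worse) | 19.3% |
| 18:30 or worse | 11.1% |

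**Cost in precision.** For a difference of two means with common variance, the variance is proportional to 1/k + 1/(48 − k) = 48 / [k(48 − k)]. Relative to 24:24, the efficiency is k(48 − k) / 576:

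- 21:27: 567 / 576 = 0.984
- 20:28: 560 / 576 = 0.972
- 18:30: 540 / 576 = 0.938

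Averaged over all splits, E[X(48 − X)] = 48 × 24 − (12 + 576) = 564, and 564 / 576 = 0.979. The mean loss is about 2%, or roughly one patient in 48.

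**Sensitivity to the assumption.** If each of the four pair types were used exactly six times, the number of A's would be 6 × 2 + 6 × 1 + 6 × 1 + 6 × 0 = 24 and the list would end at 24:24. Runs of AA or BB could still unbalance the arms along the way.

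**With balanced blocks.** If every block holds equal A's and B's and the blocks fill 48 places exactly, the split is 24:24 with certainty.

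**The case against.** The strongest reply is that little harm follows. Independent assignment with equal probability is a legitimate 1:1 randomisation. It is unbiased, the t-test planned for the primary outcome remains valid with unequal arms, and the average precision loss is about 2%. All of this stands.

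The threshold of 20 also carries limited weight. The protocol gives no power calculation behind it, so falling to 19 crosses no defined boundary. A 20:28 split still meets the requirement at randomisation, although it leaves the smaller arm no reserve for the planned loss. The probabilities also depend on a draw rule that the protocol does not state.

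A reader might infer two stronger points that the document does not support:

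- **That concealment fails for half the patients.** Under the scheme as listed, with equal-probability draws, the next letter is always an even chance, so nothing can be predicted. Predictability of 24 of the 48 allocations would arise only with AB and BA alone, which is not what the protocol lists. It would also require someone involved in enrolment to know the block size and the earlier assignments. The protocol does not say who enrols, and it has the envelopes opened by an anaesthesiologist unaware of the study.
- **That time trends during recruitment would bias the comparison.** Simple randomisation leaves such trends unconfounded in expectation; only chance imbalance remains.

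The reply does not remove the contradiction between a list described as blocked, a set of pairs that blocks nothing, and group sizes stated as 24 each.

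**Conclusion.** The point holds as an error in the description of the randomisation. That the four pairs impose no restriction is certain from the text. The probabilities of 11.5% for 24:24, 31% for 20:28 or worse and 19% for an arm below 20 before loss rest on independent, equal-probability draws. Another rule, such as equal use of each pair type, could give 24:24, but none is stated.

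The consequence is loss of guaranteed balance and an ambiguous procedure, with no bias and no breach of concealment in the scheme as listed. This should be fixed, but it is not a defect on which the trial stands or falls.

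**What to change.** In the Randomization section, replace the block description with randomly permuted balanced blocks, each containing equal numbers of A and B. State that block sizes are not disclosed to staff who enrol or treat patients, and keep them in a separate restricted randomisation file.

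Build the list to total exactly 48. Twelve blocks of 4 would do (12 × 4 = 48), as would a shuffled mix such as six blocks of 4 and four blocks of 6 (6 × 4 + 4 × 6 = 48). Drawing sizes 4 and 6 at random with no fixed total is not quite enough: with equal chances it fills 48 exactly only about 40% of the time and gives 24:24 about 77% of the time, otherwise 25:23. That imbalance is trivial, but fixing the total avoids it.

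Do not repair the text by deleting AA and BB. Fixed AB/BA blocks give 24:24, but every second allocation is then determined by the one before it, for anyone who knows the block size. Earlier assignments could be learned on the ward, since aspirin is given daily in one arm and stopped in the other, and no placebo is described.

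The cost is regenerating the list and refilling the envelopes before the first is opened. If a list is already in use, record how it was actually generated.

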**Study protocol**

Assigned ward nurses will deliver drugs to all patients during the perioperative period.

In the aspirin continuation group (n=24), aspirin (100 mg; aspirin protect®, Bayer AG, Leverkusen, Germany) will be administered every morning until the operative day.

In the aspirin discontinuation group (n=24), aspirin will be stopped 4 days before the operative day.

Other anticoagulants, such as clopidogrel or warfarin will be stopped at least 5 days before surgery in all patients.

Anesthetic and surgical techniques will be standardized during the trial. A single anesthesiologist and a single surgeon, not aware of the group assignment, will perform OPCAB in all patients. All patients will arrive in the operating room without premedication. A catheter will be inserted at radial artery after local anesthesia for continuous arterial blood pressure monitoring. And standard monitoring including ECG, NIBP, SpO_2_ and BIS monitoring. Anesthesia will be induced with 0.15 mg/kg midazolam, 1-2 μg/kg sufentanil and vecuronium. After endotracheal intubation, mechanical ventilation will be applied to maintain an end-tidal carbon dioxide tension of 35-40 mmHg. Anesthesia will be provided with target-controlled infusion of propofol and remifentanil.

Target activated clotting time (ACT) will be 250-350 s.

1.5 mg/kg unfractionated heparin will be administrated before making of Y-graft.

At following time points, blood will be sampled for evaluation of platelet activation and responsibility.

- T1. Before skin incision
- T2. After reperfusion of graft
- T3. End of surgery
- T4. 24 h postoperatively
- T5. 48 h postoperatively
- T6. 72 h postoperatively
- T7. 96 h postoperatively

**Laboratory evaluation lists**

At the time points (T1, T2, T3, T4, T5, T6, T7)

- Platelet count

- Conventional coagulation tests (CCT : INR, aPTT, fibrinogen)

- Activated clotting time (ACT)

- Capillary closure time (PFA-100/EPI, PFA-100/ADP)

- D-dimer

- von Willebrand factor

- Rotational thromboelastometry (ROTEM)

- Platelet function (Verify/Now accumetrics)

- Platelet aggregation (multiplate , inducer : collagen, ADP, TRAP-6, arachidonic acid)

- Annexin V (flow cytometry)

- platelet P-selectin (flow cytometry)

- platelet CD41(flow cytometry)

- PAC-1 (flow cytometry)

- platelet CD63( flow cytometry)

- Thromboxan B2

At the time points (T1, T6)

- GPllb, GPllla, COX-1 mRNA (RT-PCR)

